### Interventions

In this trial, we are testing a stand-alone (“pure”) Motivational Interviewing at intake (MII) intervention. MI offers the optimal platform at intake because it uses a person-centered approach to explore client needs and elicit reasons the client would want to enter treatment, to understand prior successes or challenges managing substance use (e.g., past treatment attempts), and to reinforce the values and goals that motivated the client to seek treatment in the first place. This study seeks to *replace* an Information-First assessment as the first client contact with a clinician, instead offering an opportunity to improve substance use treatment engagement by using an evidence-based intervention in the manner that is theoretically most useful and as it is used with other health problems.

### Theoretical basis for MII

The proposed “pure” MII was developed in accordance with the theory of MI [35]. MI has been shown to increase client engagement and commitment to make behavioral changes [36–38]. Specifically, MI facilitates client behavior change by prioritizing client engagement. There are two active ingredients of pure MI that, when integrated and executed effectively, demonstrate how the therapeutic process promotes client decisions to make positive changes [31]. The relational component, based on Carl Roger’s client-centered therapy [39], involves a partnership between the therapist and client, wherein the therapist is demonstrating support, curiosity, and acceptance of the client’s current presentation. The technical component, based on behavioral reinforcement principles, entails how the therapist guides the conversation around change, eliciting client ambivalence around behavior change and reinforcing client statements that align with self-identified treatment goals. As such, the benefit of MI is based on how well the therapist leverages the therapeutic process to promote clients’ autonomous changes [40, 41]. Further, MI attends to the two notable therapeutic processes identified by both clients and providers as barriers to treatment engagement: client motivation and the therapeutic alliance. Client motivation is variable during the initial contact with a treatment agency, underscoring the need to elicit and reinforce client motivations for seeking treatment now. Also, the question-answer format of the standard intake assessment makes it difficult to develop therapeutic rapport, places therapists in the role of experts, and may disengage clients from treatment. The supportive yet directive nature of a pure MII is theorized to mobilize client motivation and therapeutic alliance and, thus, increase clients’ likelihood of entering treatment, staying in treatment, and completing treatment. This approach maximizes the empirical evidence and theoretical basis for designing an initial client contact where engagement is needed.

### MII condition

Client participants randomized to the MII condition will receive a 60-to-90-min pure MI session focused on why the client wants treatment at the current time. The MI session will follow the theory of MI and involve a goal-oriented and collaborative conversation about *why* the client wants treatment now, and how treatment might fit with client concerns, goals, and values. The provider will use open questions, reflective listening, and autonomy support in a flexible, non-authoritative manner. Rather than asking specific questions in different life domains, the provider will explore with the client their desires, abilities, reasons, and needs for treatment, how treatment fits with their values, and what successful treatment would look like to them. The client’s language about change will be elicited and reinforced strategically to increase its frequency and strength across the session. The goal of the MII conditions is to help clients resolve ambivalence around entering treatment now.

### IAU condition

Client participants randomized to the IAU condition will receive the 60-to-90-min standard clinic intake focused on obtaining a complete account of the client’s current and past substance use behavior and related sequelae. In line with ASAM guidelines, the assessment is a semi-structured interview that also assesses the client’s psychosocial history and clients are asked a series of questions related to support systems, living situation, education, occupational status, family, and medical history. The IAU is a comprehensive assessment that is delivered to all clients entering IOP at both study sites.

### Intervention training and monitoring

Some providers who conduct standard intake assessments at the participating study sites will be recruited to deliver the MII intervention. We will have separate intake providers deliver the MII and IAU conditions to interested participants. The MII intake providers will participate in a two-day MI training workshop (total of 8 h). The training includes a series of activities focused on increasing trainees’ knowledge and skills in the areas of client engagement (e.g., “A Taste of MI” exercise), therapeutic partnership (e.g., “Personal Values Card Sort” exercise), reflective listening (e.g., “Complexifying Reflections”), and client language (e.g., “Identifying Change Talk”). The workshop is comprised of educational materials and experiential exercises from the Motivational Interviewing Network of Trainers (MINT) Resources for Trainers. Following the workshop, MI intake providers will complete at least three individual feedback and coaching sessions, in accordance with recommended benchmarks of quality MI training [42, 43]. Each session will be scheduled after the intake providers complete a baseline audio-recorded clinical work sample with a standardized or actual patient. The work sample will be rated using the Motivational Interviewing Treatment Integrity (MITI) [44]. The clinical trial will begin after the MII intake providers reach proficiency on the MITI from these work samples. The MII intake providers also will participate in weekly supervision during the trial to assure ongoing adherence and competence to the MII intervention. The training workshop, feedback and coaching sessions, and weekly supervision will be provided by the first and second author, both of whom are licensed clinical psychologists and members of the MINT.

### Data collection protocol

The standard phone screen that is conducted with all clients requesting addiction treatment services at the two study sites will be used to collect client demographic characteristics, substance use and mental health information, as well as to determine client eligibility. The primary outcomes are treatment entry (i.e., attends first scheduled treatment session after the intake), number of treatment sessions attended, and completion (based on review of treatment attendance and discharge records) data obtained from electronic medical records, which will be collected each month following the intake and until clients are discharged from the treatment facility (standard treatment regimen: 3 months). A trained research assistant who is masked to allocated intake condition will administer brief self-report assessments before and after the intake condition to evaluate the theorized mechanisms of client engagement. Theorized mechanisms include change in client motivation, assessed with the Readiness Ruler (RR) [45] scores and perceived therapeutic alliance assessed using the Working Alliance Inventory (WAI) [46] scores. The RR is a measure of client readiness to change, with demonstrated psychometric support and good predictive validity [45, 47]. The WAI is a widely used measure of therapeutic alliance, with demonstrated psychometric support for a three-factor structure (goals, bond, and tasks), model invariance, and good internal consistency (αs = 0.85–0.90) [48]. Personal and medical information about participants will be protected by an NIH certificate of confidentiality.

### Implementation process evaluation

For the second objective—implementation feasibility—we will collect quantitative and qualitative data, in addition to evaluating intervention fidelity (described above), on the execution of the MII to inform implementation effectiveness and sustainability in community-based addiction treatment programs. Our mixed methods design is guided by the Consolidated Framework for Implementation Research (CFIR) [32]. A semi-structured interview will be the primary data source of implementation feasibility with study-involved and study-naïve personnel participants. Additionally, we will administer an online Qualtrics-based survey before and after the clinical trial ends to examine perspectives on the MII condition among clinicians and staff at both participating sites. For study-naïve personnel participants, they will be asked to complete the online survey one time, after the clinical trial ends. The online survey will comprise a brief demographic form to capture job characteristics (e.g., client caseload) and program characteristics (e.g., program location) and three validated measures—Texas Christian University-Organizational Readiness for Change (TCU-ORC), Readiness for Organizational Change (ROC), and Change Process Capability Questionnaire (CPCQ)—selected based on a systematic review of measures that capture implementation determinants across the five CFIR domains [49] (see Table 1). The TCU-ORC [50, 51] is the most widely used and well-validated measure of organizational readiness, and is comprised of 18 subscales across four broad areas: (1) motivation for change, (2) institutional resources of the program, (3) personality attributes of the staff, and (4) organizational climate of the program. The ROC [52] is a measure of organizational readiness and is comprised of four subscales: appropriateness, management support, change efficacy, and personally beneficial. Finally, the CPCQ [53, 54] is a measure of an organization’s capability to make changes, and is comprised of four subscales: previous history of change, plans for continuous organizational refinement, ability to initiate and sustain change, and change strategies.

**Table 1 Tab1:** CFIR domains, definitions, examples, and data sources for implementation aim

Domain	Definition	Subconstruct examples	Data source
Intervention characteristics	Intervention attributes that may impact the success of implementation	Intervention source, adaptability, trialability, cost	ROC subscales map onto one subconstruct: relative advantage TCU-ORC subscales map onto one subconstruct: design quality and packaging CPCQ subscales map onto one subconstruct: relative advantage
Outer setting	Factors external to the organization that may impact intervention implementation	Patient needs and resources, external policies and incentives, peer pressure	TCU-ORC subscales map onto the following subconstructs: patient needs and resources, external policy and incentives, cosmopolitanism ROC subscales map onto one subconstruct: patient needs and resources
Inner setting	Internal factors that may impact the intervention implementation	Culture, implementation climate, compatibility, learning climate, available resources	TCU-ORC subscales map onto all subconstructs in the Inner Setting ROC subscales map onto the following subconstructs: implementation climate and readiness for change CPCQ subscales maps onto all subconstructs
Characteristics of the individuals involved	Knowledge, attitudes, perspectives, and traits of the individuals at the organization(s) involved in implementation	Knowledge and beliefs about the intervention, self-efficacy, other personal attributes	TCU-ORC subscales map onto the following subconstructs: self-efficacy and other personality attributes ROC subscales map onto the following subconstructs: knowledge and beliefs about intervention and self-efficacy
The process of implementation	Factors involved in the execution of intervention implementation	Planning, engaging, champions, reflecting and evaluating	TCU-ORC subscales map onto one subconstruct: planning CPCQ subscales map onto the following subconstructs: engaging, executing, reflecting/evaluating Individual semi-structured interviews with study-involved and -naïve personnel participants Intervention fidelity (using the MITI)

CFIR: Consolidated Framework for Implementation Research; TCU-ORC: Texas Christian University-Organizational Readiness for Change; ROC: Readiness for Organizational Change; CPCQ: Change Process Capability Questionnaire; MITI: Motivational Interviewing Treatment Integrity

### Outcomes

Clinical effectiveness is prioritized in the current study, and implementation feasibility is a secondary outcome. As such, the primary effectiveness outcome is whether clients enter the outpatient treatment program (i.e., attend their first scheduled treatment session). Secondary effectiveness outcomes include the number of treatment sessions attended and whether clients completed the outpatient treatment program. All effectiveness outcomes will be assessed using electronic medical record data and putative mechanisms of engagement will be assessed using self-report measures administered before and after the assigned intake condition. Mechanisms of effectiveness include change in client motivation and therapeutic alliance.

### Statistical analyses

#### Effectiveness outcomes

The primary effectiveness endpoints for this study will be medical record-verified client entry into treatment (completion of a 1st treatment session after the intake), number of treatment sessions attended, and client completion of treatment (i.e., based on review of treatment attendance and discharge records from assessor blind to intake condition). Analyses will be conducted using intent-to-treat principles [55], with all randomized participants included in the denominator for calculating engagement outcomes. Two binary logistic regression analyses will be used to compare the two intake conditions on the dichotomous outcomes of treatment entry and treatment completion. A negative binomial regression analysis will be used for the count outcome of number of treatment sessions attended. The following covariates will be included in each analysis: participant’s age, gender, race/ethnicity, substance use type, and pre-intake level of motivation. Further, we will explore possible therapist effects on each effectiveness outcome by performing one-way analyses of variance, specifying therapist as a random factor. We will obtain the percent of variance explained by the therapist by dividing the variance for the therapist factor by the total variance.

To evaluate mechanisms of effectiveness, separate mediation analyses will be performed on change in client motivation and therapeutic alliance on the three engagement outcomes. We will conduct logistic regression analyses for the two dichotomous outcomes and a negative binomial regression analysis for the count outcome. To explore whether observed direct effects are mediated by client motivation and therapeutic alliance, a bootstrapping method will be used (Preacher et al. 2008), providing a powerful test of mediation [56].

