**Methods:**

The study will determine the effectiveness of two intake conditions: (1) standard comprehensive intake assessment (intake-as-usual [IAU]), and (2) MII consisting of a person-centered discussion between provider and client about the client’s desire and intent to enter treatment. Although both interventions are focused on understanding client presenting complaints and needs for treatment, the delivery differs as the IAU uses a semi-structured assessment guide, while MII applies the theory of MI to have a conversation about treatment engagement. Adults seeking outpatient addiction treatment services will be randomly assigned to the MII condition (n = 75) or the IAU condition (n = 75). Primary outcomes will be client engagement (i.e., treatment entry, attendance, and completion) obtained from the electronic medical record. Secondary outcomes (client motivation and therapeutic alliance) will be putative mechanisms of client engagement assessed immediately before and after the intake. The trial also will explore determinants of effective, sustainable implementation using assessments of organizational readiness and capacity to change, as well as interviews on MII implementation feasibility.

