## Methods

### Study design

Funded by the National Institute on Drug Abuse (NIDA) as part of an initiative to improve behavioral healthcare services, the MII trial uses an HEI-1 design, where the primary outcome is clinical effectiveness, and the secondary outcome is implementation feasibility [33]. The study will be sufficiently powered to detect our primary outcome, which is the impact of the intervention on client entry in the outpatient treatment program, as well as the number of treatment sessions attended and whether client participants completed the three-month program (our secondary outcomes).

To determine clinical effectiveness, a single-blind randomized clinical trial (RCT) will be used at two community-based addiction treatment programs—one that provides in-person services and one that provides telehealth services. Eligible clients will be those scheduled for an initial intake to the outpatient programs at each site. Interested participants will be randomly assigned to receive MII or intake-as-usual (IAU) by the on-site, clinical intake providers (see Fig. 1, CONSORT diagram). To determine implementation feasibility, a mixed-methods pre-post design will be used to evaluate changes in readiness and capability to change the intake process among addiction treatment personnel at both clinical sites. Specifically, we will administer a survey comprising several measures of implementation determinants to personnel before and immediately following the RCT, as well as an individual interview after the RCT to identify key facilitators and barriers to implementation effectiveness. To understand the feasibility of changing the intake process across addiction treatment programs, we also will administer the survey and individual interview to addiction treatment personnel employed at other substance treatment programs in New Mexico (see Fig. 2 for client and personnel study procedures).

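### The protocol article names treatment entry as the sole primary outcome in two sections and three engagement outcomes as primary in three others, so the endpoint that decides the trial is not fixed

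*Protocol article*

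**What the plan says.** Two sections rank the outcomes and put entry alone at the top.

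- Study design refers to "our primary outcome, which is the impact of the intervention on client entry in the outpatient treatment program", and then lists "the number of treatment sessions attended and whether client participants completed the three-month program (our secondary outcomes" as the closing label has it.
- Outcomes states that "the primary effectiveness outcome is whether clients enter the outpatient treatment program", followed by: "Secondary effectiveness outcomes include the number of treatment sessions attended and whether clients completed the outpatient treatment program".

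Three sections give all three outcomes primary status.

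- Abstract, Methods: the primary outcomes are client engagement, spelled out as entry, attendance and completion. The label secondary goes elsewhere: "Secondary outcomes (client motivation and therapeutic alliance) will be putative mechanisms of client engagement".
- Data collection protocol: "The primary outcomes are treatment entry", with sessions attended and completion in the same list.
- Statistical analyses, Effectiveness outcomes: "The primary effectiveness endpoints for this study will be medical record-verified client entry into treatment", again with sessions and completion in the same list. This section then plans a logistic regression for entry, another for completion, and a negative binomial regression for sessions, all with the same covariates.

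The Study aims section places all three outcomes under the primary aim without ranking them.

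**The concern.** These are two incompatible hierarchies in the current text of one document. The Outcomes section and the Statistical analyses section follow one another directly and disagree. This is not a detail that the article has left to a fuller document: a statistical analysis plan written from this text would have to overrule one set of sections.

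What is at stake is the trial's verdict. Suppose entry shows no difference between MII and IAU, but completion does. Under Outcomes, the primary result is null and there is a secondary signal. Under Statistical analyses, one of the primary endpoints is positive. Someone choosing between these after seeing the results could point to the protocol for either choice, and a reader of the final report could not tell which hierarchy had been prespecified.

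**Working it through.** **Step 1. The sections side by side.**

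| Section | Entry | Sessions, completion | Motivation, alliance |
|---|---|---|---|
| Abstract, Methods | primary | primary | secondary |
| Study design | primary | secondary | not ranked |
| Data collection protocol | primary | primary | mechanisms |
| Outcomes | primary | secondary | mechanisms |
| Statistical analyses | primary | primary | mechanisms |

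Entry is primary in all five. Sessions and completion are secondary in two and primary in three. The label secondary covers different outcomes in the Abstract and in Outcomes.

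**Step 2. When the readings diverge.** The same three regressions are run under either hierarchy, so the estimates do not change. The verdict changes only when entry is not significant and sessions or completion is.

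**Step 3. Size of the effect on error.** The article gives no significance level, sidedness, familywise error rate or rule for declaring success, so there is no stated figure to reproduce. The calculation assumes a two-sided 5% level for each test and a rule that any one significant result suffices.

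- Entry as sole primary: 5%.
- Three independent tests: 1 − 0.95³ = 1 − 0.857375 = 0.1426, or 14.3%. Independence is impossible here, because a client who does not enter attends no sessions and cannot complete. The figure is therefore only an upper limit.
- Three equally correlated normal test statistics (1,000,000 draws):

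| Correlation | At least one p < 0.05 |
|---|---|
| 0.3 | 13.6% |
| 0.5 | 12.5% |
| 0.7 | 10.9% |
| 0.9 | 8.3% |

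- Simulated null trials with the nesting built in: 75 per arm (Sample size and power analysis), entry 56% in both arms (100% − 44% non-return, from Background), zero sessions for non-entrants, completers a subset of entrants, logistic and negative binomial tests without covariates. Completion among entrants and the session distribution are not in the article and are assumed.
  - Completion among entrants 30%, 50% and 70% (1,500 trials each): at least one p < 0.05 in 9.8%, 9.3% and 8.2%. In 2.5% to 4.3% of trials the false positive came with entry non-significant, which is the case in Step 2.
  - Completion among entrants 20%, 50% and 80%, maximum 12 or 36 sessions (800 trials each): 6.6% to 10.9%. The lower values arise because the negative binomial test was conservative with so many zeros.

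The nested range is thus about 7% to 11%. Against the nominal rate that is 6.6/5 = 1.3 times to 10.9/5 = 2.2 times. With 800 trials, the Monte Carlo standard error is √(0.066 × 0.934 / 800) = 0.9 percentage points at the low end and √(0.109 × 0.891 / 800) = 1.1 at the high end, so the limits are approximate.

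**The case against.** The strongest reply is that this is loose labelling in a condensed article. The same three analyses are reported whichever label applies, the Outcomes section is clear, and a multiplicity rule could sit in a statistical analysis plan that is not shown. Part of this stands: the absence of a significance level or multiplicity rule from the article is not a fault in itself, and the verdict is at risk only when entry disagrees with another outcome. It does not remove the conflict, because the article states both hierarchies outright.

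A reader might infer more than the text supports, in four ways.

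- That each outcome is tested at 5% and success on any one counts. Neither is stated. Listing several primaries does not say whether any, all or an ordered sequence must succeed.
- That error is inflated two- to threefold. The upper part of that range needs outcomes close to independent, which nesting rules out.
- That the power statement covers one outcome only. Study design claims sufficient power for entry and also for sessions and completion, and Sample size and power analysis gives one effect size tied to no named endpoint.
- That the Statistical analyses section governs because it describes the analysis. The article sets no order of precedence among its sections.

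**Conclusion.** The contradiction holds with high confidence: two sections make entry the sole primary outcome and three make entry, sessions and completion all primary. It concerns the decisive endpoint and should be settled before anyone sees results by arm.

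The effect on error is conditional. With two-sided 5% tests and a rule that any one suffices, the familywise rate is roughly 7% to 11% under nested outcomes, with session and completion distributions assumed. The 14.3% figure is a limit that this trial cannot reach. The case for correction does not depend on where in that range the truth lies, since an unfixed primary outcome permits a choice after the fact at any of these rates.

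**What to change.** Before unblinded analysis, amend the Abstract, the Data collection protocol and the Statistical analyses section to agree with Study design and Outcomes: treatment entry is the single primary effectiveness outcome, sessions attended and completion are secondary, and motivation and alliance are mechanism measures. This version fits best because those two sections are the ones that expressly rank the outcomes, and Background identifies non-return after intake as the point of highest attrition.

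If the sponsor does intend three primaries, amend Study design and Outcomes instead and state a multiplicity rule. Bonferroni at 0.05/3 = 0.0167 each, for example, gives 1 − (1 − 0.0167)³ = 4.9% under independence, and less with correlated outcomes.

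Testing the secondaries in a fixed order after a significant entry result is an option, not a requirement.

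The cost of the preferred fix is wording in three places. The sponsor gives up claiming success on sessions or completion alone.

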### Study setting

The MII trial is being conducted in two community-based addiction treatment programs, one based in New Mexico and the other based in California. These sites provide outpatient treatment services to adults with SUD. An email detailing the MII trial and requesting participation as a study site was sent to 25 eligible addiction treatment facilities. Five facilities agreed to allow staff to be contacted by researchers for the implementation portion of the trial. However, three of the facilities were unable to recruit clients for the randomized clinical trial due to competing demands (e.g., implementing changes to other treatment services). The two participating treatment facilities are community-based addiction treatment programs that have similar intake procedures for clients seeking outpatient services, though one site provides in-person services and the other provides telehealth services.

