### Study participants: recruitment, eligibility, randomization, and blinding

Client participants will be recruited from among individuals scheduled for a standard intake for the outpatient program (OP) at either of the two study sites. As part of standard procedures at both study sites, clients contact the treatment facility and complete a brief phone screener to identify their presenting concerns (i.e., substance use and mental health issues) and determine their level of care (e.g., detoxification services, OP), and are then scheduled for the intake appointment. Across both facilities, the intake appointment for clients seeking OP is the same. Clients who are scheduled for an OP intake will be recruited for study participation upon arrival to their scheduled intake appointment. Clients will be deemed eligible if they are at least 18 years old and English-speaking. Clients will be excluded from participation if they are experiencing severe withdrawal symptoms or are experiencing current symptoms of psychosis, mania, or suicidal intent. Exclusion criteria are determined through standard enrollment procedures at each site, such that clients first meet with administrative staff to complete consent for treatment paperwork and answer questions about their current need for detoxification services.

A research assistant will meet with eligible and interested participants to review the consent form, answer any questions, and assure the client that participation is not a requisite for concomitant care. Consenting client participants will be randomized to MII or IAU and randomization will be stratified by gender. The randomization sequences will be implemented (and concealed) in Redcap, a secure, customizable clinical trials management system used for data management and performed by a member of the research team who will not be involved in data collection and analytic procedures. Therefore, the principal investigator, research staff who will be conducting the informed consent and assessments, and all co-investigators will be masked to the intervention assignment. Only the designated project manager, one research assistant not involved in assessments or analyses, and the study intake therapists will not be masked to condition.

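### Site is neither a randomisation stratum nor a covariate in the effectiveness models, so a chance site imbalance between arms would shift the estimate uncorrected

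*Protocol article*

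**What the plan says.** Under Study participants, the protocol article names one stratification factor: "randomization will be stratified by gender". Under Effectiveness outcomes, the covariate list opens with "The following covariates will be included in each analysis" and names "age, gender, race/ethnicity, substance use type, and pre-intake level of motivation". It therefore covers both logistic models (entry, completion) and the negative binomial model (sessions attended). Site is in neither list.

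Study design describes the two programs as "one that provides in-person services and one that provides telehealth services", and Study setting places them as "one based in New Mexico and the other based in California". The article does not say which delivery mode belongs to which state.

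Clients are "randomly assigned to receive MII or intake-as-usual (IAU) by the on-site, clinical intake providers" (Study design), and Intervention training and monitoring assigns separate providers to each arm. The Discussion allows psychologists or graduate students to act as MII providers where site staff cannot. Therapist effects are explored by a one-way analysis of variance with therapist as a random factor and no site term. The only planned comparison across sites is under Implementation outcomes and concerns the personnel data.

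**The concern.** Entry, sessions attended and completion are all attendance outcomes, and one site delivers treatment in person while the other delivers it remotely. It is reasonable to suppose, though the article does not show it, that attendance differs between them. If it does, any chance difference in site mix between arms moves the arm contrast, and nothing in the design or the models removes that movement.

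This is not detail left to an analysis plan. The article states the stratification factor and a specific covariate list for each model, so a plan that follows it would omit site. If an imbalance then appeared, adding site would be a choice made after seeing the data.

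A secondary consequence concerns the therapist analysis. Where a provider works at one site only, a one-way analysis counts a difference between sites as variance between therapists.

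**Working it through.** **Inputs from the article.** 75 clients per arm and d = 0.24 (Sample size and power analysis). 44% of clients do not return after intake (Background), used here as a control entry rate of 56%. Two sites.

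**Inputs assumed.** Site sizes (equal, with 70/30 as a variant) and the between-site gap in entry (0 to 40 points). The article gives neither. It also states no alpha, so two-sided 5% is assumed.

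**The plan's own figure.** The article gives no figure that involves site. Its power statement supplies the effect size used below but does not reproduce: Φ(0.24 × √(75/2) − 1.96) = Φ(−0.49) = 0.31, not 0.80. That is a separate and larger problem, and adding site does not repair it.

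**1. Effect implied by d = 0.24 on entry.**
- Odds ratio = exp(0.24 × π/√3) = 1.545.
- Control odds = 0.56/0.44 = 1.273. Treated odds = 1.273 × 1.545 = 1.967, which is 66.3%.
- Difference = 66.3 − 56 = 10.3 points.

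**2. Chance imbalance in site share without site stratification.**
- SD = √(0.25 × (1/75 + 1/75)) = 0.082, so the 95% range is ±1.96 × 8.2 = ±16 points. The hypergeometric calculation gives the same 8.2.
- Probability of an imbalance of at least 10 points: 19%. At least 15 points: 5%.
- With a 70/30 split: SD 7.5 points, and probabilities 15% and 3%.

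**3. Resulting shift in the unadjusted risk difference (imbalance × gap), equal sites.**

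| Assumed gap in entry | 95% range of shift |
|---|---|
| 10 points | ±1.6 |
| 20 points | ±3.2 |
| 30 points | ±4.8 |
| 40 points | ±6.4 |

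These are 95% ranges, not maxima. At 70/30 the 20- and 30-point rows become ±2.9 and ±4.4.

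**4. Share of the total sampling error.** The standard error of the risk difference is √(2 × 0.56 × 0.44/75) = 8.1 points, a 95% range of about ±16. The shift has SD 8.2 × 0.20 = 1.6 points at a 20-point gap and 8.2 × 0.30 = 2.5 at 30. It therefore makes up about (1.6/8.1)² = 4% to (2.5/8.1)² = 9% of the variance.

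**5. Simulated power.** Logistic regression, 4,000 trials per scenario, 150 clients, equal sites, arm and site the only predictors. OR 1.545 corresponds to d = 0.24. OR 2.6 is a larger effect, chosen to show power near 75%.

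| Gap | OR | No site term | Site in model | Stratified by site, site in model |
|---|---|---|---|---|
| 20 | 1.545 | 24.8% | 24.9% | 23.9% |
| 30 | 1.545 | 22.9% | 23.5% | 23.9% |
| 40 | 1.545 | 20.8% | 21.4% | 22.1% |
| 20 | 2.6 | 74.3% | 75.8% | 75.8% |
| 30 | 2.6 | 72.4% | 74.6% | 73.8% |
| 40 | 2.6 | 68.0% | 73.4% | 73.0% |

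The Monte Carlo standard error is about 0.7 points (√(0.25 × 0.75/4000)), so the differences at OR 1.545 are mostly noise. At OR 2.6 with a 30-point gap, stratifying by site but leaving it out of the model gave 68.4%, against 73.8% with site in the model.

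**6. Type I error.** Without site stratification it stays at about 5% overall, with or without site in the model. Among null trials with an imbalance of at least 15 points and a 30-point gap, rejection was about 10% without site and 4% with it. That subset is about 5% of 4,000, or 200 trials, so these two figures are imprecise.

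**The case against.** A reader might infer that an MII effect cannot be told apart from an effect of site mix. The documents do not support that. Clients are randomised individually, so site is independent of arm in expectation. Chance imbalance in an omitted covariate is already part of the sampling error: ±3.2 points sits inside an overall range of about ±16. Overall type I error is unaffected, and at d = 0.24 adjustment gains almost no power. All of this stands, and it bounds the point.

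The strength of site as a predictor is also undocumented. No site-specific rate is given, and the article stresses similar intake procedures and a single standard regimen length. That is why the gaps above are labelled assumptions. The stated similarity, however, mainly concerns the intake appointment, whereas the outcomes are attendance at later sessions, which are delivered in different ways.

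A reader might also infer that the in-person site is the one in New Mexico, or that every provider belongs to one site. The article gives location and delivery mode separately. Its fallback MII providers are not tied to a site, so nesting of providers within site is clear only for site staff. The therapist analysis is exploratory, so mixing site into it does not touch the primary comparison.

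Finally, the smaller unadjusted log odds ratio in the simulations (0.90 against 0.99 adjusted, at OR 2.6 and a 30-point gap) largely reflects the non-collapsibility of the odds ratio, which is a change of estimand, not bias.

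None of this is a reason to leave site out. An imbalance of 10 points or more has about a one-in-five chance with equal sites, and the models as listed would not correct it.

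**Conclusion.** The omission is certain from the text; the harm is modest and depends on assumptions. With equal sites and an entry gap of 20 to 30 points, chance site imbalance would shift the arm contrast within a 95% range of ±3.2 to ±4.8 points, about a third to a half of the roughly 10-point effect implied by d = 0.24. With no site difference the shift is nil.

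This is avoidable chance error. It is neither systematic bias nor a threat to the validity of the trial. The expected power gain is about 0 to 5 points for gaps up to 40 points, and the upper end needs both a 40-point gap and an effect much larger than planned. The case for acting is that the correction is nearly free, protects against the unlucky allocation, and settles the question before the data are seen.

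**What to change.** - Add site as a fixed effect to both logistic models and to the negative binomial model. This costs one degree of freedom in each and uses data already held.
- Include site in the exploratory therapist-variance analysis, so that a site difference is not reported as therapist variance. Record which providers, if any, work at both sites.
- Report the arm effect by site descriptively, without a claim of interaction.
- If randomisation has not begun, or the sequence can still be changed, stratify the REDCap allocation by site as well as gender and keep site in the models. This costs one change to the allocation table. If the sequence is fixed, the covariate alone is enough.
- Make the change by dated amendment, or in the analysis plan, before outcome data are examined by arm.
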